## Discussion

Although social determinants are an important consideration for high-risk, medically complex care managed populations, evidence suggests that screening for social needs and providing linkages to community organizations to address identified patient unmet social needs can be hampered by barriers to enabling technologies. As health centers serving systematically underserved populations increase their capacity for documenting and addressing patients’ social needs, it is imperative to identify implementation strategies that support the adoption of enabling technologies and workflows to advance effective clinical-community linkages. While little is known about how to support implementation of technologies specifically focused on clinical-community linkages, evidence is available on implementation strategies that are effective in promoting adoption of other EHR-based tools. Refining these implementation strategies with health center input is expected to support improving the intervention’s ability to conduct social risk screening and place needed referrals among high-risk patients. This is time sensitive, as chronic disease guidelines and value-based payor models are increasingly stipulating screening, referring, and supporting receipt of services for patients’ social needs. To our knowledge, this is the first study to test a set of implementation strategies to improve clinical-community linkages among safety-net primary care health centers. Results will be disseminated to guide primary care clinics on using implementation strategies to further adoption of enabling technologies targeting social risk-targeted care via clinical-community linkages.

### Limitations and Considerations

This pragmatic trial will be conducted with a focus on one enabling technology, CR, an application in the Epic EHR. To our knowledge, CR is the first instance of a seamlessly integrated EHR module designed to meet the unique, complex needs of care coordinators providing care to health disparate patients within primary care settings. As social risk-targeted care is advanced through care guidelines and payors, it would be expected that additional applications will be developed in other EHR systems. To address this, disseminated study findings will be presented in an EHR-agnostic manner. Additionally, the study design does not directly address other known factors that influence clinical-community linkages including funding, staff resources, community organizational capacity, and patient preferences. Our team will work closely with health centers and community partners to identify the broadest possible range of internal and external factors that may influence outcomes and will consider these in results interpretation and dissemination.

## Conclusions

No prior studies have assessed how EHR-enabled clinical-community linkages can be effectively operationalized in safety-net primary care health centers. This will be the first study to develop a set of implementation strategies targeting the adoption of enabling technologies to promote social risk screening, referrals, and service receipt assessment. Results have the potential to improve clinical-community linkages and advance health equity for the over 30 million low-income and racial/ethnic minority populations cared for in community-based health centers.

### Trial Status

The study was reviewed by the Advarra Institutional Review Board (Pro00074727) which provided approval for quantitative data collection and analysis and the modified Delphi, semi-structured interviews, and guided tour of EHR that comprise formative activities. ). (Aim 1 and 2: January 15, 2024; Aim 3: October 20, 2023). The institutional review board will receive the protocol again before the pilot and main trial. No research with human subjects will be conducted until the proper approvals have been received.

## Figures and Tables

**Figure 1: F1:**
[figure not shown]
DEDICATE formative activities

**Figure 2. F2:**
[figure not shown]
CONSORT SW-CRT Flowchart Diagram

**Table 1 T1:** Study concepts and approach mapped to ITIM concepts

ITIM Concepts	Applied in study	Description
	
**INNER CONTEXT**		

Technology adoption (Dependent)	Primary Outcome	Social needs screening and referring among patients in CM programs

Implementation	Intervention	Refinement and testing of implementation strategies will address technology-driven facilitators and barriers to align clinic environment, needs, and policies with clinical-community linkages

Technology	EHR application targeted by intervention	Enabling technology (CR) has been adopted to facilitate linkages to community organizations. The intervention will optimize technology and workflows to support clinical-community linkages

Interfacing systems	EHR application targeted by intervention	Clinical-community linkages should be user-friendly and seamless

Workflow old	Analysis	Qualitative analysis will assess old workflows and identify areas for optimization of clinical-community linkage workflows

Workflow new	Intervention	Practice facilitation is a key implementation strategy of the intervention

Users (adopters)	Analysis	Understanding user needs through health center engagement will inform refinement of intervention

Leadership	Intervention	Championship is a key implementation strategy of the intervention

Communication	Intervention	Audit & Feedback and implementation support by Practice Coach, Champion, and Trainers are key implementation strategies of the intervention

**OUTER CONTEXT**		

Accreditation/regulation	EHR application targeted by intervention	Reimbursement of social needs screening, referral and community organization linkage are important components of CM and emerging value-based care programs

Economic environment	Outcome	Clinics will need to demonstrate their ability to support clinical-community linkages to be competitive for emerging value-based care contracts

Facilitators	Intervention	Broad health center partner engagement will inform implementation strategies that will comprise the intervention to improve clinical-community linkages

Vendor	EHR application/tools targeted by intervention	Epic is an EHR vendor and tool developer that supports the operationalization of clinical-community linkages

**Table 2 T2:** Role of formative activities on refining implementation strategies

Implementation strategy	*Formative activities will provide needed input in the following areas to refine the intervention for live testing in health centers*:		
	Content	Format	Cadence
**Dedicated training** to foster adoption and efficient use of enabling technologies to support social needs care coordination activities(34)	- Topics to cover at initial training - Ongoing training content	- Individual or group - Synchronous, asynchronous or hybrid	- Length of initial training - Frequency of booster trainings
**Clinic champions** promote buy-in and engagement by building internal support and mobilizing resources(87)	- Recruitment criteria for champion - Scope of champion role	- On-site assessment of adoption by users - Communication preferences with study team	- Hours per week needed to accomplish champion activities
**Practice coaches** facilitate workflow redesign to optimize adoption of enabling technologies(88)	- Focus within one department or across departments - Coordinate with ongoing internal and external initiatives to screen, refer, and ascertain receipt of services	- Individual or group - Synchronous, asynchronous or hybrid	- Hours of initial practice coaching support needed by health center - Frequency of meetings through implementation
**Audit & feedback** reports show progress and evidence needed to facilitate benchmarking and motivate users(89)	- Determine data to display to show progress and adoption of enabling technologies and receipt of community services (closed-loop referrals)	- Use of graphs, tables, and text to convey information	- Frequency of report creation, distribution, and review

**Table 3 T3:** Stepped-wedge design

					Year 1	Year 2		Year 3				Year 4				Year 5			
Q1	Q2	Q3	Q4	Q1	Q2	Q3	Q4	Q1	Q2	Q3	Q4	Q1	Q2	Q3	Q4	Q1	Q2	Q3	Q4
Wedge 1 (Health Centers 1–4)					Formative Intervention Refinement	C	C	I	F	F	F	F	F	F	Analysis and Dissemination				
Wedge 2 (Health Centers 5–8)						C	C	C	I	F	F	F	F	F					
Wedge 3 (Health Centers 9–12)						C	C	C	C	I	F	F	F	F					
Wedge 4 (Health Centers 13–16)						C	C	C	C	C	I	F	F	F					
Wedge 5 (Health Centers 17–20)						C	C	C	C	C	C	I	F	F					

Note: C = Control condition, I = Intervention condition, F = Follow-up.

**Table 4 T4:** Outcomes Per RE-AIM Framework.

RE-AIM Outcome	Outcome Type	Measure
Reach	Primary	binary outcome of whether the patient has been screened for unmet social needs
Effectiveness	Primary Secondary Secondary	binary outcome of whether the patient with an unmet social need received a referral to a community organization to address an identified social need binary outcome of controlled hypertension binary outcome of controlled diabetes
Adoption	Secondary	binary outcome of receipt of community services (closed-loop referral) among patients with a social need who were referred to community organizations
Implementation	Secondary	*assessed through qualitative methods
Maintenance	Secondary	*assessed through qualitative methods

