## Abstract

**Background:**

Adverse social determinants of health contribute to health inequities. Practice guidelines now recommend incorporating patient unmet social needs into patient care, and payors increasingly reimburse for screening and providing related referrals to community organizations. Emergent electronic health record (EHR)-based tools can enable clinical-community linkages, but their adoption commonly faces workflow and infrastructure barriers. Targeted implementation support such as training, championship, practice facilitation, and audit and feedback, can enhance such tools’ adoption, but no prior research has assessed such strategies’ impact on the adoption of ‘enabling technologies’ supporting clinical-community linkages. This study will test whether providing targeted implementation support to safety-net primary care health center care management teams improves the sustained adoption of EHR-based enabling technologies used to 1) screen for social needs and 2) link patients to community organizations.

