## Methods

### Setting

This study will be conducted among health centers that are members of OCHIN, Inc., a multi-state network of community health organizations that serve more than 6 million people in rural and medically underserved communities nationwide. OCHIN is a national nonprofit health IT consultancy that provides a fully hosted and shared EHR platform with tailored tools and expertise, including practice management tools, to > 1,000 care delivery sites across 30 states. While all OCHIN members share a single instance of the Epic EHR, each is an independent organization with its own governing board. Conducting this study in a diverse group of health centers improves the likelihood that its results will be generalizable to other primary care settings, an important feature of pragmatic trials.

OCHIN Epic includes a robust suite of tools designed to support collecting and acting on social risk data, many developed through NIH-funded studies.(28, 49–54) One such tool, CR, was made available to OCHIN members in 2022. CR is an integrated EHR tool that supports comprehensive care coordination for high-touch care management, including assessing patients’ social needs, making referrals to community organizations, and tracking referral outcomes to ascertain receipt of community services. Yet at present, an estimated < 10% of health centers use these functionalities to make referrals and track referral outcomes.

All OCHIN health centers that have activated the CR tools in their EHR and participate in one or more CM, population health, or value-based payment model programs that require care coordination of social needs for patients will be eligible for the trial. Such programs include CMS’s care management programs, CalAIM, and patient-centered medical home (PCMH) programs. At least 42 OCHIN member health centers met these criteria at study start-up (November 2023) and another six had adopted CR tools by March 2024. We anticipate that even more health centers do so and thus be eligible for recruitment in early 2025.

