### Inclusion criteria

Trial health centers will be recruited from OCHIN members that use CR for at least one care management or population health program that stipulates care coordination to address unmet social needs for a monthly average of ≥ 15 enrolled patients. Trial centers must also have care management staff to support programming and provide primary care.

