### Analyses

Primary outcomes will be measured at six time points for each health center: at baseline and at the end of each of the five wedge’s receipt of the intervention during the CRT. At each time point, all active CM patients receiving care management in a CR program that incorporates social risk activities (e.g. CalAIM, CCM) will be included. The analyses use an open cohort design, as some patients will be measured across multiple time points and others only once. We will identify whether each eligible patient has been screened. We will also identify if patients who screened positive for a social need were referred to a community organization; to the extent possible we will also identify which patients with social needs declined offered referrals. Currently, there is large variability in whether health centers collect data on patients who decline referrals. We will guide on collecting this information as part of implementation support, and we will investigate if we can assess declined referrals as part of our analyses. As the main outcomes are binary and patients are nested in health centers, we will use generalized linear mixed models with a binomial distribution and a logit link and include a random effect for the health center. Patient-level covariates will include age, race/ethnicity, gender, federal poverty level, insurance type, care management program (e.g. CCM; CalAIM), and a health center-level indicator of treatment arm (intervention or control) for each time point.

The analysis for closed-loop referral (secondary outcome) will be limited to patients enrolled in CM that received a referral to a community organization for a social need. Clinical outcomes of hypertension and diabetes control will be limited to enrolled patients with hypertension and/or diabetes, respectively, and a medical visit during the measurement period.

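### Table 4's Adoption outcome is service receipt among patients already referred, so it can stay flat or fall while use of the tool rises, and it conflicts with Table 1

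*Protocol article*

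**What the plan says.** The abstract states the aim as testing whether implementation support "improves the sustained adoption of EHR-based enabling technologies used to 1) screen for social needs and 2) link patients to community organizations".

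Two tables then say what represents adoption:

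- Table 1 (ITIM concepts) lists technology adoption as the dependent concept, ties it to the primary outcome, and describes it as "Social needs screening and referring among patients in CM programs".
- Table 4 (RE-AIM outcomes) places screening under Reach and referral under Effectiveness. Its only entry for Adoption is the secondary outcome "binary outcome of receipt of community services (closed-loop referral) among patients with a social need who were referred to community organizations".

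The Analyses section confirms the analysis set for that outcome: it is "limited to patients enrolled in CM that received a referral to a community organization for a social need".

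Three other places bear on the reading. The Setting section counts "tracking referral outcomes to ascertain receipt of community services" among the functions of Compass Rose (CR). The hypothesis in the Background section has better adoption leading on to screening, referrals and receipt of services. The audit-and-feedback row of Table 2 names adoption of the technology and receipt of community services as two separate things to display.

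**The concern.** Adoption of a tool is a question about use: do care management teams screen, refer and track with it? The Table 4 measure starts after one of those steps has already happened. A patient who should have been referred through the tool and was not is outside the denominator, so failure to use the referral function cannot lower the score.

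Referral is also something the intervention is designed to change. The referred patients in the control and intervention periods are therefore different selections of patients, and their closure rates are not a like-for-like comparison. If support leads teams to refer patients who are harder to connect, the rate falls because the tool is used more.

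Receipt further depends on whether the community organization has capacity and whether the patient takes up the service. The Limitations and Considerations section lists both among the factors that the design does not directly address.

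At stake is the reported RE-AIM Adoption result, which could come out null or negative after a successful rollout.

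**Working it through.** **Plan's own figures.** The article states no number for the Adoption row. Its only related figure is power above 80% for the referral outcome. A stepped-wedge calculation (20 centers, five sequences, six periods, both autocorrelations 0) reproduces this. For 48% to 63.3% at an intraclass correlation of 0.15, power is 0.88 with 163 patients per center-period, or 0.825 if 163 is spread over six periods. For 48% to 72% at 0.30, it is 0.94 or 0.93. Those figures are sound as bounds and do not bear on this point.

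**Inputs.**
- Referral rate before support r0 = 48%; after support r1 = 63.3% or 72% (Sample Size Calculation).
- Patients in the referral denominator: 163 per center (same section).
- Range of referral rates in the literature: 10% to 86% (same section).
- Closure rate among referred patients: not given. Assumed c = 60% for referrals that would be made anyway, unchanged by the intervention, and q = 60%, 40% or 20% for added referrals.

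**Effect of added referrals.**
Table 4 measure after support = [r0 × c + (r1 − r0) × q] / r1.
Closed loops per patient with a need = r0 × c + (r1 − r0) × q.

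Before support these are 60% and 0.48 × 0.60 = 28.8%.

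With q = 40%:
- r1 = 63.3%: 0.288 + 0.153 × 0.40 = 0.349 per patient with a need; 0.349 / 0.633 = 55%.
- r1 = 72%: 0.288 + 0.24 × 0.40 = 0.384 per patient with a need; 0.384 / 0.72 = 53%.

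| Closure of added referrals | Table 4 measure, r1 = 63.3% | Per patient with a need | Table 4 measure, r1 = 72% | Per patient with a need |
|---|---|---|---|---|
| 60% | 60% | 38.0% | 60% | 43.2% |
| 40% | 55% | 34.9% | 53% | 38.4% |
| 20% | 50% | 31.9% | 47% | 33.6% |

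The pattern does not depend on these particular values. With c held fixed, the Table 4 measure is unchanged when q = c and falls whenever q < c, while closed loops per patient with a need rise whenever q > 0.

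**Between centers.** Take 163 patients with a need in each of two centers, with the ends of the article's referral range and assumed closure rates of 80% and 40%:
- Low user: 10% referred = 16, of whom 13 close. Table 4 measure 13/16 = 81%; per patient with a need 13/163 = 8%.
- High user: 86% referred = 140, of whom 56 close. Table 4 measure 56/140 = 40%; per patient with a need 56/163 = 34%.

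**Centers with no referrals.** Such a center-period has no record in this outcome. The chance of no referral among n patients is (1 − r)^n. With n = 27 (163/6):
- r = 48%: about 2 × 10⁻⁸
- r = 10%: about 6%
- r = 2%: about 58%

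With n = 163 per period and r = 2%, it is about 4%. At the planned rate this is negligible; it matters only if recorded referral is rare.

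**The case against.** A reader might infer that the trial cannot answer its adoption question. The documents do not support that. Table 1 assigns technology adoption to the two primary outcomes. The Analyses section measures screening in all active care management patients and referral in those who screened positive. Neither conditions on a referral, so a center that screens patients and finds needs but refers nobody scores zero on referral.

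A reader might also infer that most centers would vanish from the control-period Adoption analysis, because the Setting section says "an estimated < 10% of health centers use these functionalities to make referrals and track referral outcomes". Applied to 20 centers, 10% would leave 20 × 0.90 = 18 without data. That step fails for three reasons. The figure is not an estimate for trial centers, which must already "use CR for at least one care management or population health program". The outcome is referral to a community organization and is not restricted to referrals made in CR. And at the planned 48% referral rate, empty center-periods are negligible.

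Three further arguments have some force:
- Tables 1 and 4 apply different frameworks, so one outcome may sit under different names. That excuses the primary outcomes being called Reach and Effectiveness. It does not explain why receipt of services is called Adoption when the hypothesis and Table 2 treat the two as distinct.
- Recording a closed loop uses CR's tracking function, so the row does capture some use. But it mixes that with referral volume, organization capacity and patient uptake. If support improves tracking, the measure could also rise, and these influences could not be told apart.
- The trial does not rank centers, and in a patient-level model a center with few referrals carries little weight. The two-center contrast is therefore only an illustration. The fall produced by added referrals occurs within each center's own patients, and neither weighting nor a center random effect removes it.

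**Conclusion.** The point holds for the Adoption row of Table 4 and no further. The row is mislabelled: it conditions on an outcome that the intervention targets, can move against tool use, and disagrees with Table 1.

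Under the assumed closure rates of 60% and 40%, it would fall by about 5 to 7 percentage points while closed loops per patient with a need rise by about 6 to 10 points. The size rests on closure rates that the article does not give, and on closure of existing referrals staying constant. The direction requires only that added referrals close less often than existing ones; equal closure gives no change at all despite more use.

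No primary outcome or power figure is affected. What is affected is the RE-AIM Adoption conclusion. The Outcomes section ties neither primary outcome specifically to CR, so as the article stands no quantitative outcome directly counts use of the tool.

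**What to change.** 1. In Table 4, move closed-loop receipt to Effectiveness. Keep the rate among referred patients, and also report it per patient with an identified need. That second denominator matches the referral primary outcome; it still depends on screening, which should be said when it is reported.
2. Define Adoption as CR use, computed for every center at every time point, with centers that record none counted as zero. Report it by function: CR-recorded screening, CR-recorded referral, and CR-recorded referral-outcome tracking. Active care management patients are a denominator that does not depend on earlier use of the tool. A single any-use composite is less useful, because referrals follow a positive screen and it would largely repeat the screening outcome.
3. Analyse these measures in the same stepped-wedge model as the other binary outcomes.
4. Align Tables 1 and 4, or add a note explaining how the ITIM and RE-AIM uses of adoption correspond.

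The cost is small. The Data section already plans to extract CR activity from the EHR, so this means revised table wording and a few derived variables. The downside is one or a few more secondary outcomes to derive and report.
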